### Data management {18a} {19} {27}

Source data will be recorded using paper case report forms (CRFs) which will then be double-entered into a password-secure electronic database. The CRFs and database will be routinely checked for accuracy by the investigators during the data collection period. The final database will be locked after resolution of all queries. All paper CRFs will be filed and kept in lockable cabinets in offices accessible only to study personnel. At the conclusion of the study, the files will be transferred to the Tropical Diseases Research Centre where they will be stored for a period of 5 years after study completion.

### Participant retention and withdrawal {18b}

To facilitate retention in the study, participants will be issued study visit cards that include the dates of their follow-up visits. We will collect participants’ telephone numbers and physical addresses to allow the study team to contact participants in case of missed visits, advising them to report to the clinic for their scheduled visit within the window period of 3 days. Participants are allowed to leave the study at any time for any reason without any consequences. Participants will be withdrawn from the study only if they withdraw informed consent.

### Statistical analysis {20a} {20b} {20c}

Longitudinal data will be displayed using the nonparametric Kaplan-Meier estimations of the survival function. The primary analysis will be comparison of the 42-day incidence of MIP using multivariate models to estimate the relative hazard between the IPTp-SP and IPTp-SP+ groups according to intention-to-treat (ITT). Testing for proportionality of hazards will be done using formal statistical testing with Schoenfeld residuals as well as visual inspection of the nonparametric survival estimates. For non-proportional hazards, an extended Cox model will be applied. To handle interval censoring due to participants who miss one or more follow-up visits, we will use parametric models for interval-censored survival-time data. The relative hazard will be estimated in parametric models accounting for recurrent events by using a robust variance estimator. For the primary safety analysis, we will compare the proportions of serious and non-serious AEs using logistic regression models and relative hazards of AEs using Cox regression methods as above. Secondary analyses of continuous outcomes (hemoglobin concentration, birthweight) will be examined in linear regression models and in logistic regression models for binary outcomes (prevalence of low birth weight, neonatal mortality, placental malaria, congenital malaria, maternal anemia, congenital anemia, drug resistance allele frequency). Prespecified subgroup analyses will be done according to the following strata: primigravidae, multigravidae, gestational age at enrollment, delivery before or after the day 63 visit, treatment dose on a mg/kg basis, positive *P. falciparum* PCR on enrollment, and presence or absence of quintuple and sextuple mutations. In a secondary analysis, we will compare the proportions of treatment failures and prevention failures according to the antimalarial drug given at the first encounter (SP or DP) in an on-treatment analysis using logistic regression. Treatment failures will be defined as recurrent infections that are determined by genotyping to be recrudescent parasites from the initial infection in participants who tested positive by PCR at the initial visit. Prevention failures will be defined as PCR-confirmed parasitemia in participants who initially tested negative by PCR at the first visit, or who tested positive by PCR at the first visit but who experienced reinfection with a new parasite as determined by genotyping. No interim analysis is planned. Every effort will be made to collect complete data for all participants and minimize missing data. Missing data will be handled using multiple imputation.

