**Methods:**

This is a protocol for a phase IIIb open-label, two-armed randomized controlled superiority trial to assess the safety and efficacy of a hybrid approach to IPTp combining screening and treatment with dihydroartemisinin-piperaquine (DP) to the current IPTp-SP regimen at the first antenatal care clinic visit. Pregnant women without HIV infection and without signs or symptoms of malaria will be randomized to either standard IPTp-SP or hybrid IPTp-SP plus screening and treatment (IPTp-SP+). In the IPTp-SP+ arm, participants who screen positive by rapid diagnostic test for *P. falciparum* will be treated with DP at the first antenatal visit while those who screen negative will receive SP per current guidelines. All participants will be administered SP on days 35 and 63 and will be actively followed biweekly up to day 63 and then monthly until delivery. Infants will be followed until 1 year after delivery. The primary endpoint is incident PCR-confirmed MIP at day 42. Secondary endpoints include incident MIP at other time points, placental malaria, congenital malaria, hemoglobin trends, birth outcomes, and incidence of adverse events in infants up to the first birthday.

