### Trial objectives {7} {12}

This research protocol is designed to assess the safety and efficacy of a revised IPTp schedule that incorporates a screen-and-treat strategy using RDT and DP at the first antenatal care visit (IPTp-SP+). The research objectives and corresponding endpoints are listed in Table 1.

**Table 1 Tab1:** Outcomes

Objectives	Outcomes/endpoints
Primary objectives	
To compare the effectiveness of IPTp-SP versus IPTp-SP+ for treating and preventing maternal *P. falciparum* infection To compare the safety and tolerability of IPTp-SP versus IPTp-SP+	• Relative hazard of *P. falciparum* infection diagnosed by PCR at day 42 after randomization (primary outcome) • Relative hazard of *P. falciparum* infection diagnosed by PCR or microscopy at days 14, 28, 35, 42, 63, delivery, and 1-month post-partum in infants • Proportion who experience at least one episode of *P. falciparum* infection by day 14, 28, 35, 42, or 63 • Proportion with treatment or prevention failure at day 42 stratified according to study drug (SP or DP) • Median time to first episode of MIP • Acute, chronic, and prior placental infection at delivery • Medication-related adverse events and serious adverse events until 1-year post-partum (primary outcome)
Secondary objectives	
To compare the effectiveness of IPTp-SP versus IPTp-SP+ for reducing complications of MIP	• Mean birth weight and prevalence of low birth weight (within 72 hours post-partum), neonatal mortality (within 28 days post-partum), congenital malaria diagnosed by PCR, placental malaria diagnosed by histopathology using placental biopsies, maternal anemia (hemoglobin changes at days 14, 28, 42 and 63), congenital anemia, Incidences of pregnancy losses, congenital *P. falciparum* infection
To compare selection for drug resistant parasites between infected individuals in the IPTp-SP and IPTp-SP+ treatment groups	• Relative allele frequencies of genotypic markers of drug resistance in malaria parasites
To measure piperaquine exposure and duration	• Terminal elimination half-life of piperaquine determined by noncompartmental analysis of drug concentrations at 0, 14, 28, 35 and 42 days

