### Clinical procedures {11d} {13} {15} {26a}

Study procedures are outlined in Table 3 and the flow of events is shown in Fig. 1. The informed consent will be administered by a study nurse in the local language (Bemba) and/or in English as preferred by the participant. Assent will be obtained from participants <18 years old, and informed consent will be obtained from those ≥18 or the legally authorized representative for minors. If the participant cannot provide a written signature, then a thumbprint will be obtained. After collection of demographic data, provision of informed consent, baseline medical and obstetric history, and physical examination by a study physician including eligibility assessment, participants will be randomized to either the IPTp-SP or IPTp-SP+ treatment groups. All participants will undergo hemoglobin measurement as part of the screening process. On enrollment, fingerstick blood will be drawn for preparation of dried blood spots (DBS) for subsequent molecular testing. In addition, participants randomized to the experimental group (IPTp-SP+) will undergo RDT.

**Table 3 Tab3:** Schedule of events

	Antenatal period *Study day*									Postpartum period *Study month*			
Event	0	1–2	14	28	35	42	63^a^	Unsch.	Birth	1	6	9	12
Informed consent/oral assent	•												
Medical history	•												
Physical examination, including height, weight, temperature	•		•	•	•	•	•	•	•				
Fetal viability	•		•	•	•	•	•	•	•				
Focused history and examination			•	•	•	•	•	•	•	•	•	•	•
Adverse event evaluation	•	•	•	•	•	•	•	•					
IPTp-SP^b^	•				•		•						
RDT^c^	•												
Treatment with DP^d^	•	•											
DBS for PCR, genotyping	•		•	•	•	•	•	•	•				
Malaria microscopy^e^			•	•	•	•	•	•	•				
Hemoglobin measurement	•		•	•		•	•		•	•			
Blood sample for PK^d^	•		•	•	•	•							
Delivery									•				
Placental biopsy, cord blood									•				
Infant assessment including history and exam, weight, heel stick									•	•	•	•	•

^a^Monthly visits continue until delivery

^b^Includes participants randomized to standard IPTp-SP, participants randomized to IPTp-SP+ who test negative at the first visit, and all participants in both groups at days 35, 63 and then monthly until delivery

^c^Limited to participants randomized to IPTp-SP+

^d^Limited to participants randomized to IPTp-SP+ who test positive by RDT at the first visit

^e^Only participants with signs or symptoms of malaria will undergo microscopy

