**Fig. 1 Fig1:**
[figure not shown]
Study flow diagram. *ANC*, antenatal care. *DP*, dihydroartemisinin-piperaquine. *IPTp-SP,* intermittent preventive treatment in pregnancy with sulfadoxine-pyrimethamine with (+) or without screen-and-treat. *RDT*, rapid diagnostic test for *P. falciparum* infection

Treatment with either SP or DP will be administered as described above. Participants will return for follow-up on days 14, 28, 35, 42, and 63 and then monthly thereafter until delivery. They will be instructed to report to the clinic for any illness between scheduled visits.

At each scheduled or unscheduled visit, the study clinician will perform an interval history and physical examination, including an updated medication history. During the active follow-up period (up to day 63), DBS will be collected and hemoglobin will be measured. SP will be given on days 35 and 63. Additional doses of SP will be given during monthly visits until delivery with a minimum of 4 weeks between doses and laboratory samples (e.g., blood slide for microscopy, urinary tests, full blood count) will be collected if clinically indicated according to signs and symptoms. Antimalarials or antibiotics with antimalarial activity (e.g., systemic erythromycin, macrolide antibiotics, trimethoprim-sulfamethoxazole or other sulphonamides, tetracyclines, quinolones, clindamycin) will be prohibited during the active follow-up period.

Participants who present during the follow-up period with any signs or symptoms of malaria will undergo testing by thick smear, and DBS will be collected from those with positive microscopy. The signs and symptoms that we will consider indicative of possible clinical malaria include fever, chills, weakness, fatigue, myalgia, arthralgia, headache, anorexia, nausea, vomiting, abdominal pain, or diarrhea. All confirmed uncomplicated malaria cases will be treated with artemether-lumefantrine according to national guidelines (Coartem™ 20 mg/120 mg four tablets taken at 0, 8, 24, 36, 48, and 60 h). Participants who develop severe malaria defined according to WHO criteria will be referred to SPGH for inpatient management [20].

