On the day of delivery, the participant and infant will be evaluated as soon as possible after delivery. The birthweight will be measured, and an assessment for congenital abnormalities will be done. Obstetric complications including but not limited to hemorrhage, premature rupture of membranes, cesarean section, and others will be captured as adverse events. Congenital abnormalities, if present, will also be recorded. Thick and thin peripheral blood films, DBS, and hemoglobin measurement will be done on both the participant and infant. In addition, cord blood, placental blood films for thick and thin smear microscopy, placental DBS, and placental biopsy for histopathological analysis will be collected.

Infants will be reassessed at 1, 6, 9, and 12 months postpartum for focused history and physical examination, including interval medication and hospitalization history, growth, and assessment of developmental milestones. At the first monthly visit, hemoglobin measurement and malaria parasitology by thick smear and PCR testing using DBS prepared from heel stick blood will be performed.

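### Hemoglobin and maternal anemia are repeated outcomes, but the plan names only linear and logistic regression, with no within-woman correlation, day-0 covariate or lead contrast

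*Protocol article*

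**What the plan says.** All references are to the protocol article.

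- **Method, continuous.** The Statistical analysis section says: "Secondary analyses of continuous outcomes (hemoglobin concentration, birthweight) will be examined in linear regression models". Birthweight is one value per infant; maternal hemoglobin is not one value per woman.
- **Method, binary.** Maternal anemia is to be examined "in logistic regression models for binary outcomes (prevalence of low birth weight, neonatal mortality, placental malaria, congenital malaria, maternal anemia", in the same list as outcomes observed once.
- **Outcome.** Table 1 (Trial objectives) lists "maternal anemia (hemoglobin changes at days 14, 28, 42 and 63" under the secondary effectiveness objective. The abstract calls the endpoint "hemoglobin trends".
- **Data.** Baseline is available for everyone: "All participants will undergo hemoglobin measurement as part of the screening process" (Clinical procedures). For follow-up the same section says: "During the active follow-up period (up to day 63), DBS will be collected and hemoglobin will be measured". Table 3 schedules hemoglobin at days 0, 14, 28, 42 and 63 and at birth, and for delivery the text adds: "Thick and thin peripheral blood films, DBS, and hemoglobin measurement will be done on both the participant and infant". So a fifth maternal value after baseline exists, although the Table 1 endpoint names four.
- **Dependence handled elsewhere.** The Statistical analysis section names a robust variance estimator for recurrent infections. The section on plasma piperaquine concentrations names mixed effects models. Neither is extended to hemoglobin or anemia.

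**The concern.** One model family is assigned both to an outcome measured once and to an outcome measured repeatedly in the same woman. Where the article plans for dependence within a woman it says so, and for hemoglobin and anemia it does not. A reader therefore cannot tell whether the visits enter one model, what happens to their correlation, or which comparison is the hemoglobin result. Day-0 hemoglobin, known for every woman, is not named as a covariate.

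Maternal anemia is one of the complications that the secondary effectiveness objective asks about. At stake are the error rate or precision of that comparison, and whether it yields one answer or several.

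**Working it through.** The article gives no standard deviation, correlation, effect size or power for hemoglobin, so there is no stated figure to reproduce.

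**Inputs.** From the article: m = 4 post-baseline visits (Table 1), 162 evaluable women per arm and two-sided alpha 0.05 (Sample size calculation). Assumed: equal variance (set to 1) and equal correlation rho between any two visits including day 0, and no true arm difference for the error rates. Range for rho: 0.3–0.8, or 0.3–0.7 where stated.

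**Reading 1: visits pooled, no correlation term.** Naive SE / true SE = 1/√(1 + (m−1)rho). True level = 2[1 − Φ(1.96 × ratio)].

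| rho | 1 + 3rho | SE ratio | true level |
|---|---|---|---|
| 0.3 | 1.9 | 0.73 | 15.5% |
| 0.5 | 2.5 | 0.63 | 21.5% |
| 0.7 | 3.1 | 0.57 | 26.6% |
| 0.8 | 3.4 | 0.54 | 28.8% |

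Simulation (4,000 trials, 162 per arm) gave 22.7% at rho 0.5. Analysing one mean per woman brought it back to 4.5%. For change scores, two visits share the subtracted baseline, so their correlation is (1 − rho)/[2(1 − rho)] = 0.5 whatever rho is, and the level is about 21.5% throughout (simulated 22.2%, 21.6% and 22.2% at rho 0.3, 0.5 and 0.7).

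**Reading 2: arm-by-time trend, no correlation term.** Naive SE / true SE = 1/√(1 − rho): 1.20 at rho 0.3, 1.41 at 0.5, 2.24 at 0.8. The error runs the other way: the test is conservative and loses power.

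**Reading 3: one regression per visit.** Each standard error is valid. The chance of at least one false positive among four 5% tests was 17.1%, 16.4% and 13.7% in simulation at rho 0.3, 0.5 and 0.7. Four independent tests would give 1 − 0.95⁴ = 18.5%.

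**Use of baseline, single visit.** Variance is 2(1 − rho) for a change score and 1 − rho² with baseline as covariate. The reduction is 1 − (1 + rho)/2 = (1 − rho)/2: 35% at rho 0.3, 25% at 0.5, 10% at 0.8.

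**Use of baseline, mean of four visits.** Unadjusted variance U = (1 + 3rho)/4; change score U + 1 − 2rho; covariate-adjusted U − rho².

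| rho | change score | adjusted | reduction |
|---|---|---|---|
| 0.3 | 0.875 | 0.385 | 56% |
| 0.5 | 0.625 | 0.375 | 40% |
| 0.7 | 0.375 | 0.285 | 24% |

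The two sets of reductions differ because the contrasts differ. They apply to an arm difference at one visit or averaged over visits. In a pure arm-by-time contrast the woman's baseline cancels.

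**The case against.** The strongest reply is that the article never says the visits are stacked in one model. It speaks of regression models in the plural, and Table 1 lists the outcome by day. One regression per day fits that wording and gives valid standard errors. That stands: a reader might infer that the hemoglobin standard errors will be too small, but this follows only if visits are pooled without a correlation term. For a trend, the abstract's word, the naive standard error is too large instead.

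Second, a reader might infer that baseline is ignored. Table 1 speaks of changes, so day-0 hemoglobin already enters as a change score. Change scores and covariate adjustment are both unbiased under randomisation, so what remains is a loss of efficiency, not a bias.

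Third, covariance structure, covariates and contrasts for a secondary outcome are often left to the analysis plan, and the Randomization and masking section refers to a final analysis plan that is not shown. This limits the weight of the point but does not remove it. The article does name a method for these outcomes, and it names methods for dependence where it intends them. A better method than the one named is available from data already scheduled.

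**Conclusion.** The point holds as a low-cost improvement to a secondary analysis. The method named does not match the repeated outcome in Table 1, and each way of applying it has a drawback: a true level of about 15–29% if pooled, a standard error 1.2–2.2 times too large for a trend, or four valid tests without a lead result. Which of these would occur cannot be determined from the article, so it does not support a claim that false positives will be inflated. The firmest part is efficiency: covariate adjustment beats a change score for a single-visit or average difference at every rho considered.

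All sizes rest on an assumed rho, equal correlation and equal variance across visits. The arithmetic is for the continuous outcome; for anemia the same reasoning applies, but no figure was computed. The primary endpoint and the sample size are not affected.

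**What to change.** In the Statistical analysis section and the final analysis plan:

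- Analyse hemoglobin at days 14, 28, 42 and 63 in one linear mixed model for repeated measures, with fixed effects for arm, visit, arm-by-visit and day-0 hemoglobin, and within-woman correlation through an unstructured covariance or a random intercept.
- Name one contrast as the hemoglobin result, for example the average arm difference over the four visits. Report visit-specific differences as supportive.
- For maternal anemia at repeated visits, use logistic GEE clustered on the woman and adjusted for day-0 hemoglobin.
- Keep ordinary regression for birthweight.

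The cost is wording and standard software, with no new data. Confidence intervals will be wider than those from a pooled regression that ignores correlation, but they will be valid. The Trial status section reports data collection still ongoing, and statisticians are to stay masked until the final analysis plan is approved and the database locked. On the article's account, the change could be made before unmasking.

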## Background and rationale {6a} {6b}

Malaria poses a major public health risk to pregnant women residing in areas of high *Plasmodium falciparum* transmission [1]. Pregnant women face greater risk of infection and infection-related complications compared to other adults [2]. In high burden areas, malaria in pregnancy (MIP) is usually asymptomatic and is linked to a variety of adverse outcomes including maternal anemia, maternal and perinatal mortality, congenital infection, fetal growth restriction, low birth weight, pre-term birth, and miscarriage [2–5]. The World Health Organization (WHO) therefore recommends intermittent preventive treatment in pregnancy (IPTp) with sulfadoxine-pyrimethamine (SP) to reduce MIP and associated complications in high malaria transmission areas [6].

IPTp relies on contact with patients during scheduled antenatal care clinic (ANC) visits at 4- to 6-week intervals. Treatment doses of antimalarial medication are presumptively administered without prior malaria laboratory testing to clear any potential existing infection and, for a limited post-treatment duration, to protect against subsequent infection [6]. IPTp-SP has been essential in reducing MIP-associated adverse outcomes, with the greatest impact seen when at least three doses of SP are administered throughout a pregnancy [7, 8]. However, the efficacy of SP is waning due to expanding drug resistance [9].

Resistance to SP is caused by point mutations in the genes encoding dihydropteroate synthase (*dhps*) and dihydrofolate reductase (*dhfr*) [10]. Recent studies show that in areas with high prevalence of *dhps* K540E quintuple mutations IPTp-SP effectiveness is reduced but remains associated with increases in birth weight and maternal hemoglobin compared to no IPTp-SP [11, 12]. However, studies from Tanzania and Malawi found that *dhps* A581G sextuple mutations are associated with a greater risk of low birth weight and high peripheral parasitemia, and increased placental infection and inflammation [9, 13]. In Zambia, evidence points to increasing SP resistance and a corresponding increase in breakthrough parasitemia [14, 15]. The prevalences of quintuple and sextuple mutations were estimated to be 17–61% and 2–3%, respectively, in our northern Zambia study site, and were associated with SP failures of 26% and 22% [14, 15].

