### Study population {10} {15}

Pregnant women in the second and third trimesters attending routine ANC visits at the study health facilities will be systematically screened for potential enrollment. Inclusion and exclusion criteria are listed in Table 2. All volunteer pregnant women presenting to the ANC for the first time of their current pregnancy will be assessed for eligibility according to the following criteria: age ≥15 years, estimated gestational age 16–26 weeks, hemoglobin concentration ≥7 g/dL, ability to provide informed consent, residence in the study area with intention to deliver at the health center, no evidence of clinical malaria or other acute illness, and ability to tolerate oral medication. Women will be deemed ineligible for any of the following: infection with human immunodeficiency virus (HIV) or unknown HIV status, prior IPTp-SP or other antimalarial use or antimicrobials with antimalarial activity during the current pregnancy, intolerance to either of the study drugs, existing or prior obstetric complications, prior enrollment in the study or concurrent enrollment in another study, concurrent medications with potential for drug-drug interactions or potentiation of cardiac arrhythmia, presence of chronic illness or other factor deemed likely to influence the pregnancy outcome, or other reason which is judged by the investigator to render the individual unsuitable for study participation.

**Table 2 Tab2:** Inclusion and exclusion criteria

Inclusion criteria	
• Ability and willingness to provide informed consent^a^	
• Gestational age of 16 to 26 weeks at enrollment	
• Asymptomatic on presentation, with or without a positive RDT test result^b^	
• Age ≥15 years	
• Residence within the study catchment area and no intent to move out of the study catchment area before delivery or to deliver outside of the catchment area	
• Willingness to adhere to all study requirements including to deliver at the health facility	
• Ability to take oral medication	
Exclusion criteria	
• Infection with HIV at enrollment or unknown HIV status^c^	
• History of IPTp-SP or other antimalarial drug use during the current pregnancy	
• History of intolerance or allergic reaction to any of the study drugs	
• History of known pregnancy complications or bad obstetric history including pre-existing illness likely to cause complication of pregnancy such as repeated abortions, stillbirths or eclampsia	
• Hemoglobin concentration <7 g/dL	

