### Intervention {11a} {11b} {11c}

The intervention will consist of IPTp-SP with or without screen-and-treat using DP at the first ANC visit. Participants randomized to the IPTp-SP+ group who test positive by rapid diagnostic test (RDT) will be given a full treatment course of DP (D-ARTEPP® 40 mg/320 mg three tablets daily for 3 days; Guilin Pharmaceutical) under direct observation (DOT) by a study nurse (day 0) or community health worker (days 1–2). All other participants will be treated with SP at the first visit, including those in the IPTp-SP+ arm with a negative RDT result, and all participants in both groups will be given SP at all subsequent visits (day 35, day 63, then monthly until delivery) under DOT. IPTp-SP will be administered according to national guidelines (G-SCOPE® 1,500 mg sulfadoxine/75 mg pyrimethamine for one dose no fewer than 4 weeks between doses; Guilin Pharmaceutical). Participants will be observed for 1 h post-dose to monitor for vomiting or other adverse reactions. If vomiting occurs within 30 min, the full dose will be readministered. If vomiting occurs after 30 min, half of the total dose will be readministered. In the case of persistent vomiting, the participant will be withdrawn from the study and referred for alternative treatment.

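### The prespecified subgroup by delivery before or after day 63 is defined by a post-randomisation event that, by recorded dating, can only be preterm birth or pregnancy loss

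*Protocol article*

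**What the plan says.** The Statistical analysis section names seven strata for prespecified subgroup analyses. Four are fixed at baseline and raise no issue: primigravidae, multigravidae, gestational age at enrolment, and PCR status on enrolment. The other three are "delivery before or after the day 63 visit, treatment dose on a mg/kg basis" (two strata) and "presence or absence of quintuple and sextuple mutations".

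The passages that determine what these three mean are:

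- **Entry (Table 2):** "Gestational age of 16 to 26 weeks at enrollment".
- **Visits (Clinical procedures, after Fig. 1):** "Participants will return for follow-up on days 14, 28, 35, 42, and 63 and then monthly thereafter until delivery".
- **Window (Participant retention and withdrawal):** missed visits are to be made up as a "scheduled visit within the window period of 3 days".
- **Dose (Intervention):** both drugs have a fixed adult dose. DP is "40 mg/320 mg three tablets daily for 3 days", given only to women in IPTp-SP+ with a positive RDT. Everyone else receives a single fixed dose of SP at the first visit.
- **RDT (Clinical procedures and Table 3):** done only in the IPTp-SP+ arm.
- **Mutations (Background):** "The prevalences of quintuple and sextuple mutations were estimated to be 17–61% and 2–3%, respectively".

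**The concern.** A subgroup analysis keeps the protection of randomisation only if membership is settled before treatment can influence it. Whether a woman delivers before day 63 is settled weeks after treatment starts, and after the day 42 primary endpoint. The Background names preterm birth and miscarriage among the consequences of malaria in pregnancy, so membership may depend on both the allocated strategy and the infection it is meant to prevent.

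If IPTp-SP+ prevents some malaria-related early deliveries, the early-delivery stratum in that arm will hold relatively more women who delivered early for other reasons. The two arms within the stratum then contain different kinds of women, and a difference between them cannot be read as a treatment effect. For birth weight, a secondary outcome, the stratum is tied to the result directly through prematurity. The complementary stratum is also selected, though less so because it holds most of the trial.

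What is at stake is spurious effect modification carrying the authority of a prespecified analysis, in a trial that intends to inform guidelines.

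**Working it through.** The protocol gives no figure for these subgroups, so there is none to reproduce. The checks use its entry range, visit schedule and recruitment total.

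**1. Gestational age at the day 63 visit**

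Formula: gestational age at enrolment + 63 days, plus up to 3 days for the window. The comparison point is 37w0d = 259 days, the usual preterm limit, assumed because the article does not define preterm.

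| Entry | Day 63 | With +3 days |
|---|---|---|
| 16w0d (112 d) | 175 d = 25w0d | 25w3d |
| 26w0d (182 d) | 245 d = 35w0d | 35w3d |
| 26w6d (188 d) | 251 d = 35w6d | 254 d = 36w2d |

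All are below 259 days. To reach 37w0d by day 63, a woman would have to enter at 259 − 63 = 196 days = 28w0d, or at 259 − 66 = 193 days = 27w4d with the window. Both lie outside the inclusion range. By recorded dating, the early-delivery stratum therefore holds only preterm births and losses.

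**2. Tolerance for dating error**

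The Study population section calls gestational age estimated. For a term birth to fall in the stratum, the recorded age would have to be too low by at least 259 − 245 = 14 days for entry at 26w0d, 259 − 251 = 8 days for entry at 26w6d, or 259 − 254 = 5 days for entry at 26w6d with the full window. This can occur only near the top of the entry range.

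**3. Size of the stratum (illustration)**

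The article gives no rate for early delivery or loss. At assumed rates of 1%, 2%, 5% and 10% of the 392 recruited women, the stratum holds about 4, 8, 20 and 39 women over both arms. At the lower rates it is also too small to analyse.

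**4. Dose in mg/kg**

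With a fixed dose, mg/kg = constant ÷ weight, so within one drug it only re-orders women by weight. Across arms the constant changes. At an illustrative 60 kg, SP gives 1,500 ÷ 60 = 25 mg/kg of sulfadoxine, and DP gives 3 × 320 ÷ 60 = 16 mg/kg of piperaquine per day (48 in total). All controls are on the first scale. The IPTp-SP+ arm is split between the two scales by an RDT that controls do not have. A common cut-off would partly sort women by drug, and so by RDT result, in one arm only.

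**5. Mutation stratum**

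The subgroup list gives no sampling time. If 22–26% of women are PCR-positive at entry (the prevalence quoted under Sample size calculation) and 2–3% of those infections carry the sextuple haplotype:

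- low: 392 × 0.22 × 0.02 = 1.7
- high: 392 × 0.26 × 0.03 = 3.1

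That is about 2 to 3 women in the whole trial. The prevalence input is uncertain: the Background, citing the same two sources, gives 26% and 22% as SP failures associated with the mutations. At an assumed 50% prevalence the count is 392 × 0.50 × 0.02–0.03, or about 4 to 6 women.

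**The case against.** The strongest reply is that only one of the seven strata is clearly post-randomisation, and that the rest are sound or depend on how gaps are filled. Much of this stands.

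- **Mutations.** A reader might infer that this stratum conditions on the primary endpoint, because the secondary objectives compare haplotypes among women with incident infection. The documents do not support that inference. The wording belongs to a separate objective, Table 3 schedules day-0 dried blood spots for genotyping in all participants, and the subgroup is listed directly after PCR status on enrolment. A baseline reading is natural, and sampling time is a detail an analysis plan may settle. Only a request for clarification remains. A sparse stratum limits precision but is not an error in the plan.
- **Dose.** Weight is measured on day 0 in both arms. If dose strata were formed within each drug, they would amount to weight strata. The difficulty arises only if one mg/kg scale is pooled over SP and DP, which the text neither states nor excludes. What stands is that women given DP have no counterpart on the same scale in the control arm. Day-0 weight removes the ambiguity.
- **Gestational age.** A reader might add 9 weeks to 26 and conclude that every delivery in the stratum is before 35 weeks. That is too tight: entry at 26w6d gives 35w6d, and the window extends this to 36w2d. The conclusion of preterm by recorded dating survives.
- **Impact.** These are subgroup analyses, and no confirmatory conclusion rests on them.

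None of this answers the delivery-timing point. The stratum is named in the protocol and is post-randomisation on any reading.

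**Conclusion.** The point holds for the delivery-timing subgroup. With day 63 at 25w0d to 35w6d (at most 36w2d), the early-delivery stratum consists, by recorded dating, of preterm births and pregnancy losses. The Background links both to malaria in pregnancy, and Table 1 lists losses as a secondary outcome. Arm comparisons within it are not randomised comparisons. This rests on 37 weeks as the preterm limit and on recorded gestational age; misdating at the top of the entry range could admit an occasional term birth.

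The mg/kg subgroup is a lesser point: it is ambiguous across arms but easily replaced. The mutation subgroup needs clarification only. The expected 2 to 3 sextuple carriers depend on the assumed 22–26% prevalence, though the number stays small at 50%.

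It would be wrong to infer that the subgroup plan as a whole is post-randomisation, or that the trial's main result is compromised. Gravidity, gestational age at enrolment and enrolment PCR are proper baseline strata, and neither the primary intention-to-treat comparison nor the sample size is affected.

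**What to change.** - **Delivery timing.** Remove this subgroup. Women who deliver or lose the pregnancy before day 63 contribute follow-up time up to that event. Report early delivery and loss as outcomes by randomised arm. Gestational age at enrolment is already on the list and serves as the baseline subgroup.
- **Dose.** Replace mg/kg with day-0 body weight, compared by randomised arm.
- **Mutations (clarification).** State that genotypes come from the day-0 sample of women PCR-positive at enrolment, compared by randomised arm. Give sextuple carriers as counts without a treatment contrast.

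The cost is a few lines in the analysis plan. Day-0 weight, day-0 dried blood spots and delivery dates are already collected in both arms. The Randomization and masking section keeps statisticians masked until the DSMB has approved the final analysis plan and the database is locked. Data collection was still ongoing according to Trial status, so the change can be made and documented before unmasking.
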